## Abstract

**Aims:**

The majority of patients with severe aortic stenosis (AS) planned for transcatheter aortic valve implantation (TAVI) are elective outpatients. During the COVID-19 pandemic, the time between the heart team’s decision and TAVI increased due to limited healthcare resources. We therefore implemented telemedical approaches to identify AS patients at risk for clinical deterioration during the waiting time. The purpose of the prospective, randomized, controlled ResKriVer-TAVI study (DRKS00027842) is to investigate whether a digital concept of telemedical interventional management (TIM) in AS patients waiting for TAVI improves the clinical outcomes. In the present article, we report the study protocol of the ResKriVer-TAVI trial.

**Methods:**

ResKriVer-TAVI will enroll AS patients planned for elective TAVI. Randomization to the TIM group or standard care will be made on the day of the heart team’s decision. TIM will include a daily assessment of weight, blood pressure, a 2-channel electrocardiogram, peripheral capillary oxygen saturation, and a self-rated health status until admission for TAVI. TIM will allow optimization of medical therapy or an earlier admission for TAVI if needed. Standard care will not include any additional support for patients with AS. All patients of the TIM group will receive a rule-based TIM including standard operating procedures when a patient is crossing prespecified values of a vital sign.

**Results:**

The primary endpoint consists of days lost due to cardiovascular hospitalization and death of any cause within 180 days after the heart team’s decision. Major secondary endpoints include all-cause mortality within 365 days, the number of telemedical interventions, and adherence to TIM. Follow-up visits will be conducted at admission for TAVI as well as 6 and 12 months after the heart team’s decision.

**Conclusions:**

ResKriVer-TAVI will be the first randomized, controlled trial investigating a telemedical approach before TAVI in patients with AS. We hypothesize that primary and secondary endpoints of AS patients with TIM will be superior to standard care. The study will serve to establish TIM in the clinical routine and to increase the resilience of TAVI centers in situations with limited healthcare resources.

## Introduction

Moderate to severe aortic stenosis (AS) is one of the most prevalent valvular heart diseases in the elderly, reaching a prevalence of 2.8% in patients aged ≥75 years (1). AS is associated with high morbidity and mortality; the mean survival of patients with untreated severe AS is 2 years (2). According to current guidelines, therapy of AS comprises surgical or transcatheter aortic valve implantation (TAVI) (3). In recent years, a growing number of TAVI procedures have been performed globally and, according to current recommendations, the indication for TAVI has been extended to younger and low-risk patients (3, 4). This was associated with an increase in waiting times for elective AS outpatients (5). In many centers, the waiting time between the heart team's decision and intervention exceeds 1 month. In addition, the COVID-19 pandemic resulted in limited resources also affecting TAVI procedures (6). During this period, many patients with AS stayed untreated at home and were kept on a waiting list. TAVIs were performed according to symptoms and severity of AS versus available hospital resources (7). Albassam et al. observed a mortality of approximately 5% during a median waiting period of 84 days (8). In addition to reported mortality, untreated severe AS may exacerbate and lead to decompensated heart failure (9).

Telemedical interventional management (TIM) may reduce morbidity and mortality among patients with AS. TIM, including a wide range of devices, is well studied as an outpatient management of patients with heart failure (10–14). In the TIM-HF2 trial, the remote patient management (RPM) comprised non-invasive TIM, treatment of heart failure and comorbidities, close cooperation with primary care physicians, and patient education, and was used for a maximum follow-up period of 393 days (15). In this specific patient cohort, the RPM reduced days lost to unplanned cardiovascular hospitalizations and all-cause deaths compared to standard care (15).

Despite a lack of evidence, national cardiac societies recommended the establishment of TIM in valvular heart disease during the COVID-19 pandemic (7, 16). Comprehensive TIM may address the healthcare gap during the waiting period between the day of the heart team's decision to inpatient admission for TAVI in patients with AS in times of limited healthcare resources but also under normal conditions when waiting times are long due to increased demand. Therefore, we implemented telemedical approaches to identify AS patients at risk for clinical deterioration during the waiting time. The purpose of the ResKriVer-TAVI study is to investigate whether a digital concept of telemedical interventional management (TIM) in AS patients waiting for a TAVI improves the clinical outcome of these patients. Here, we report the study protocol of the ResKriVer-TAVI trial.

## Methods

The ResKriVer-TAVI study (DRKS00027842) is a single-center, prospective, parallel-group randomized, controlled, superior, open-label trial started in 2022 at the Charité—Universitätsmedizin Berlin, Germany, and complies with the Declaration of Helsinki. The study is approved by the institutional ethics committee (EA1/017/22) and financially supported by the German Federal Ministry for Economic Affairs and Climate Action, Berlin, Germany.

We will enroll patients with AS recommended to undergo TAVI by our local heart team. AS will be defined and assessed according to the guidelines of the European Society of Cardiology (ESC) and the European Association for Cardio-Thoracic Surgery (EACTS) (3). Patients with an inability or unwillingness to measure daily vital signs (e.g., dementia, blindness, deafness, or wheelchair use) and patients enrolled in other interventional trials will be excluded from the study. Patients with AS will be screened for eligibility during their outpatient visit or hospital stay for AS assessment followed by a baseline visit after the patients have provided signed informed consent. Diagnostic work-up to grade AS and evaluate patients for TAVI or surgical approach will include medical history, laboratory measurements, echocardiography, electrocardiogram, coronary angiography, and computed tomography as a part of clinical routine. On the day of the heart team’s decision, patients will be randomized to TIM and standard care or standard care alone. Standard care will not include any additional support for patients with AS who are on the waiting list. Stratified randomization will be performed using an automatic randomization tool considering three covariates: male vs. female, age ≤80 years vs. age >80 years, and NYHA class ≤ II vs. NYHA class ≥ III. Data management will be completed in electronic case report forms.

### Study objective

We hypothesize that patients with AS who are monitored by TIM during the waiting period will demonstrate significantly fewer days lost to cardiovascular hospitalization and all-cause mortality compared to standard care during the 180 days after the heart team's decision (primary endpoint). Secondary endpoints are listed in Table 1. Follow-up visits are planned at admission for TAVI, 180 days, and 365 days after the heart team's decision (Figure 1). The study duration for each patient will be 365 days after the heart team's decision (day 1-day 180: assessment of primary and secondary endpoints, day 181-day 365 evaluation of survival status).

**Table 1 T1:** Primary and secondary endpoints of the ResKriVer-TAVI study.

Primary endpoint
• Days lost to cardiovascular hospitalization and all-cause mortality 180 days after the heart team's decision
Secondary endpoints
• Days lost to cardiovascular hospitalization 180 days after the heart team's decision • Days lost to all-cause mortality 180 days after the heart team's decision • All-cause mortality 180 days after the heart team's decision • All-cause mortality 365 days after the heart team's decision • Number of unplanned cardiovascular hospitalizations 180 days after the heart team's decision • Number of hospitalizations due to heart failure decompensation 180 days after the heart team's decision • Number of interventions by TIM • Number of hospital admissions as recommended by telemedical physicians and nurses • Patients’ adherence to TIM • Postponement of TAVI due to medical reasons (reported in days) • Quality of life assessed by PROMIS-29 + 2 questionnaire (at baseline, admission for TAVI, 180 days after heart team decision) • NYHA class (at baseline, admission for TAVI, 180 days after heart team decision) • Laboratory measurements including GFR (at baseline, admission for TAVI, 180 days after heart team decision)

TIM, telemedical interventional management; TAVI, transcatheter aortic valve implantation; PROMIS, patient-reported outcomes measurement information system (17, 18); NYHA class, New York Heart Association class; GFR, glomerular filtration rate.

**Figure 1 F1:**
[figure not shown]
Flow chart of the ResKriVer-TAVI study. TAVI, transcatheter aortic valve implantation; TIM, telemedical interventional management.

### Intervention

After randomization to the TIM group, telemedical devices will be installed by specialized nurses in patients’ homes, and measurements will be performed daily until hospital admission for TAVI. Therefore, the duration of TIM will be a varying period of approximately 21–42 days. TIM includes three sections: patient education, telemonitoring of vital signs, and telemedical interventions (Figure 2).

**Figure 2 F2:**
[figure not shown]
Overview of telemedical interventional management at patients’ homes (purple box), telemedicine center (orange box), and their interaction with the healthcare system (blue box). AS, aortic stenosis; TAVI, transcatheter aortic valve implantation. Parts of the figure were drawn by using pictures from Servier Medical Art. Servier Medical Art by Servier is licensed under a Creative Commons Attribution 3.0 Unported License (https://creativecommons.org/licenses/by/3.0/).

Patient education, performed by specialized nurses, has the aim to impart knowledge in the use of telemedical devices and the patient's disease. Patients receive the TIM devices at the beginning of monitoring and are trained regarding their use and benefits. Patients will be motivated to record vital signs every day, which is supported by a manual on how to perform measurements. Moreover, information on valvular heart disease, including possible symptoms, medical consultation, and behavior in an emergency, but also on nursing, medical, and social aspects will be provided. Examples of training include instruction on devices, guidance on medication and fluid intake, as well as lifestyle modifications tailored to specific questions and needs of the patient, and will be performed using a structured script. Additionally, a nursing assessment form will be utilized to determine the necessity for assistance and the potential provision of aids such as a wheelchair. This will be followed by advice on preventative programs and homecare; if necessary, required information on further care will be provided and external support services will be arranged. The education will involve the patient's family and caregivers.

All patients of the TIM group will receive a rule-based TIM including standard operating procedures when a patient is crossing prespecified values of vital signs (Table 2). Telemonitoring of vital signs will comprise a daily assessment of weight (A&D Precision Health Scale Model UC-352BLE, Oxfordshire, OX14 1DY, United Kingdom), blood pressure (A&D UA-651BLE Medical blood pressure monitor, Oxfordshire, OX14 1DY, United Kingdom), a 2-channel electrocardiogram (PhysioMem® PM 100, Gleisdorf, Austria), peripheral capillary oxygen saturation (Beurer PO 60 Bluetooth, Fürth, Germany), and a self-rated health status using a tablet. The self-rated health status includes a standardized scale ranging from “much worse” to “much better” (six grades), providing patients with a simple and easily understandable categorization. The medical devices are provided by GETEMED (Teltow, Germany), validated for telemedical use, and CE-certified. Data will be transmitted securely every day via mobile network, transferred to electronic patient files of the telemedicine center, and evaluated by experienced physicians and nurses. Patients with vital signs out of range will be assessed first and pathological parameters will be validated by a telephone call.

**Table 2 T2:** Prespecified values of vital signs used for TIM.

Heart rate	<50 bpm or >100 bpm
Systolic blood pressure	<90 mmHg or >140 mmHg
Diastolic blood pressure	<40 mmHg or >90 mmHg
Weight gain	>1 kg within one day
	>2 kg within three days
	>2.5 kg within eight days
Oxygen saturation	<94%
Health status	Statement of the patient that his/her condition is “worse” or “much worse” compared to the previous day

Values can be adjusted individually for each patient. TIM, telemedical interventional management.

Analysis of daily vital signs forms the basis for telemedical interventions. In the case of pathological values, recommendations and interventions will be executed depending on the severity of symptoms. Interventions may involve adjusting medication and optimizing therapy for comorbidities in accordance with current guidelines. Moreover, physicians can refer patients to a specialist at an outpatient or emergency department or admit patients earlier for TAVI due to symptom progression. Examples of medical adjustments include changes in antihypertensive or diuretic treatment, often in collaboration with the patient's primary care physician. Additionally, patients will be able to contact the telemedicine center by phone in case of emergencies or medical issues on a daily basis (from 8:00 a.m. to 4:00 p.m.). Subsequently, expert medical advice will be provided, and if necessary, appropriate measures will be initiated. Vital data will be regularly assessed to determine whether TAVI treatment can be individually delayed for each patient or if there is a need for it to be expedited.

### Statistical analysis

Overall, we plan to enroll 200 patients with AS according to the number of TAVI procedures performed at the Deutsches Herzzentrum der Charité (DHZC), Berlin, and the calculated statistical analysis throughout a study period of 2 years. In detail, 1,250 TAVIs are performed at DHZC annually, 370 of these are treated by the team of the Department of Cardiology, Angiology, and Intensive Care Medicine (the primary enrolling center)—including urgent (∼30%) and elective cases (∼70%). Only elective patients will be eligible for the study. Additionally, we are approximating an enrolment rate of 50%–75%. A difference of 6.7 days in lost days between the intervention group and the standard care group is estimated to be clinically significant and can be reached for the primary endpoint with a two-sided *t*-test, a standard deviation of 16.9, an alpha of 0.05, and a power of 0.8 in a study cohort of 200 patients. This is a sufficiently large and realistic effect.

The primary endpoint will be adjusted for stratification variables of randomization (sex, age, and NYHA class) using ANCOVA with lost days as a dependent variable and intervention group as the main effect. Adjusted means with 95% confidence intervals will be reported. This analysis will have an increased power compared to the *t* test. The primary analysis will be conducted in the full analysis set according to the intention-to-treat principle. If the requirements for parametric analysis are not met, the primary endpoint will be evaluated non-parametrically (Friedman test, rank-based ANOVA). All other endpoints will be analyzed according to their distribution with adequate tests, and estimators will be calculated with a 95% confidence interval. An exploratory analysis will be conducted.

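### The plan lets the observed data replace the primary comparison of mean days lost with a rank test, which the 6.7-day hypothesis and the 80% power do not cover

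*Protocol article*

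**What the plan says.** The primary endpoint in Table 1 of the protocol article is "Days lost to cardiovascular hospitalization and all-cause mortality 180 days after the heart team's decision". Under Methods, "patients will be randomized to TIM and standard care or standard care alone", so there are two independent parallel groups.

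The Statistical analysis section sizes the trial with a two-sided t-test: "A difference of 6.7 days in lost days between the intervention group and the standard care group is estimated to be clinically significant", with "a standard deviation of 16.9, an alpha of 0.05, and a power of 0.8 in a study cohort of 200 patients". The primary analysis adjusts for sex, age and NYHA class, "using ANCOVA with lost days as a dependent variable and intervention group as the main effect". It adds: "Adjusted means with 95% confidence intervals will be reported".

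The next step is conditional: "If the requirements for parametric analysis are not met, the primary endpoint will be evaluated non-parametrically". The methods named for that case are "Friedman test, rank-based ANOVA".

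**The concern.** The target of the primary analysis depends on the data. ANCOVA compares mean days lost, which is the quantity in the hypothesis and the sample size. A rank test asks whether patients in one arm tend to rank lower. It gives a death that costs 150 days little more weight than a long hospital stay. The two can disagree, and which is favoured depends on how the intervention works.

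Days lost will be strongly skewed: many patients at zero or at one short stay, and a few deaths far out. On the most usual reading of the condition, the analysis the trial was sized for would be displaced. At stake are what the confirmatory test addresses, whether the stated power applies to it, and whether the choice is settled before results are known.

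**Working it through.** **1. The plan's own figure.** Inputs from the Statistical analysis section: difference 6.7, SD 16.9, two-sided alpha 0.05, power 0.80. The allocation ratio is not given; 1:1 is assumed.

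n per arm = 2 × (1.960 + 0.842)² × 16.9² / 6.7² = 2 × 7.849 × 285.61 / 44.89 = 99.9, so 100 per arm and 200 in total. Power at 100 per arm is 0.800 (0.797 with the exact noncentral t). The figure reproduces, for a comparison of means.

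**2. Can days lost be normal with this SD?** The floor is 0. For a normal variable, P(below 0) = Φ(−mean / 16.9).

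| Mean days lost | Share below zero |
|---|---|
| 10 | Φ(−0.592) = 28% |
| 15 | Φ(−0.888) = 19% |
| 20 | Φ(−1.183) = 12% |

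To have only 2.5% below zero the mean would have to be 1.96 × 16.9 = 33 days. Deaths add a right tail of up to 180 days.

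**3. What the switch does when there is no effect.** Simulated trials, 100 per arm, 4,000 per scenario; ANCOVA with three binary covariates, the same model on ranks, and Shapiro-Wilk on the ANCOVA residuals as the check. The event rates are assumptions, because the article gives none for this population: 180-day mortality 0–5%, unplanned stay in 0–30%, and a TAVI stay averaging 7 days either counted or not. The SDs ran from 4 to 24.

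- Normality rejected: 100% of trials in all six scenarios, including one with no deaths and no unplanned stays.
- Type I error: ANCOVA 3.5–5.4%; rank analysis 4.5–5.7%; the two-step rule identical to the rank analysis.
- Type I error if the smaller of the two p-values were taken: 7.4–9.4%.

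**4. Power of the two analyses** (same set-up, 3,000 trials each, assumed effects; a TAVI stay is counted in all three):

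| Assumed effect, control to intervention | Mean difference | ANCOVA | Rank |
|---|---|---|---|
| Mortality 8% to 2%; unplanned stay 30% to 20% | 6.3 days | 50% | 35% |
| Unplanned stay 50% to 20%, mean length 18 to 14 days; mortality 3% to 2% | 7.1 days | 72% | 92% |
| TAVI stay 9 to 6 days only | 2.9 days | 16% | 88% |

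The first two rows have mean differences close to the planned 6.7 days, yet rank-test power runs from 35% to 92%. ANCOVA is also below 80% there, because the arm SDs (29.2 and 16.0; 22.5 and 16.7) average more than 16.9. These rows compare the two tests; they do not re-estimate the power of the planned design.

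**5. The fallback.** The Friedman test compares treatments within matched or repeated blocks, with one observation per treatment in each block. Here each patient has one value and belongs to one arm. If the 2 × 2 × 2 = 8 strata were taken as blocks, each would hold on average 200 / 8 = 25 patients, so the standard test would still not fit.

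**The case against.** The condition speaks of requirements for parametric analysis and does not name normality. At 100 per arm the mean comparison kept its type I error at 3.5–5.4% despite the skew, so a statistician could hold that the requirements are met and keep ANCOVA. How and when the check is made is ordinary content for an analysis plan that is not shown here, and its absence is no fault. This stands. A reader might infer that ANCOVA will never be the primary analysis; the text does not support that beyond the normality reading.

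A reader might also infer that the switch inflates type I error. If it always fires, it does not: the analysis is in effect a fixed rank test. The 7–9% arises only if the more favourable result is chosen, which the article does not permit. Nor does the open-label design show that the check would be made with knowledge of the difference between arms.

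The confidence intervals are not necessarily lost either. The sentence on adjusted means is unconditional, so they could still be reported, though beside a p-value that does not test them.

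Finally, one can build a case in which the rank test nearly fails: waiting deaths falling from 5% to 0 gave power of 0.55 for the t-test and 0.12 for the rank test. The article does not support that as a typical case. Its Introduction cites about 5% mortality for a median wait of 84 days, whereas the Intervention section expects about 21–42 days. At a constant hazard (an assumption), 1 − 0.95^(21/84) = 1.3% and 1 − 0.95^(42/84) = 2.5%. With deaths on average at mid-wait, preventing all of them saves about 0.013 × 169.5 = 2.2 to 0.025 × 159 = 4.0 days, short of 6.7. In other scenarios the rank test is the stronger one by a wide margin.

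What remains is the stated rule. Both readings of it are available once the data are in, and they lead to different primary analyses.

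**Conclusion.** The point holds and should be fixed. The article states a data-dependent replacement of its primary analysis. Under an ordinary normality check, the replacement occurs in essentially every trial. The test then no longer addresses the 6.7-day mean difference, and the 80% power does not carry over to it. Under the large-sample reading ANCOVA remains, so the choice is unsettled until the data are seen.

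The departure from normality follows from the article's own SD and the bounds of the endpoint. The power figures rest on assumed event rates and show only that the rank test may do much worse or much better than ANCOVA. The sample size of 200 is arithmetically correct, and either analysis alone holds about 5%. The Friedman test is the wrong method for this design on any reading.

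**What to change.** Delete the conditional switch and the Friedman test, and fix one primary analysis before outcome data are seen. The choice that matches the stated hypothesis and sample size is the strata-adjusted ANCOVA difference in mean days lost, whatever the distribution, with a robust or bootstrap 95% confidence interval. If wanted, the p-value can come from a permutation test within strata. Report a stratified rank test as a pre-specified sensitivity analysis.

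A stratified rank test as primary would also be defensible, but it would need its own effect estimate and its own power calculation.

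The cost is a change of wording and a few lines of code; N stays at 200. The downside should be stated openly: if the benefit comes mainly through fewer or shorter hospital stays, the rank test could have considerably more power than the ANCOVA.
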